### 10.3 Data Management

Processes will be employed to facilitate the accuracy of the data included in the final report. These processes will be detailed in the trial specific Data Management Plan. Coding and validation will be agreed between the trial team and the trial database will be signed off once the implementation of these has been assured.

For the DESTINY trial, CRFs will be an electronic record completed at site (except for Serious Adverse events which will be paper), only by those at site delegated the task of doing so. Forms will be considered “complete” once all data fields have been either completed unambiguously or it has been made explicit that the data is unobtainable. In all cases it remains the responsibility of the site’s PI to ensure that the CRF has been completed correctly and that the data are accurate. This will be evidenced by the electronic signature of the site’s PI on the CRF.

#### 10.3.1 Source Data

The local trial team can collate data to be entered onto the electronic database using paper copies of the data forms as worksheets, for simplicity. Where data exists in written form prior to this collation, the original record is the source data. If the data is written directly onto the worksheet, without any previous written record, the worksheet itself becomes the source data. The local team need to have a consistent approach to the use of worksheets so that it is clear if they are to be considered source data or not.

Source data may be checked against the CRFs where on-site monitoring is conducted and must be available for verification.

#### 10.3.2 Data Clarification

Missing and ambiguous data will be queried using a Data Clarification system in line with the **DESTINY Data Management Plan** and will focus on data required for trial outcome analysis and safety reporting. Single data entry with central monitoring will be employed. Staff at site (as delegated on the **DESTINY Site Signature and Delegation Log**) will enter and submit data, with the exception of serious adverse events, using an online electronic CRF at <https://www.trials.bham.ac.uk/DESTINY>. Unique log-in usernames and passwords will be provided to those who wish to use the online system and who have been delegated the role of CRF completion as detailed on the **DESTINY Site Signature and Delegation Log**. These unique log-in details must not be shared with other staff and in no circumstances should staff at sites access the trial database using another person’s login details. The trial office will be unable to edit data forms entered by site staff. The system will include data validations to improve data quality (e.g. to prevent nonsensical dates or numerical values). Changes to the data on the system will be documented and attributable, with a reason for the change documented and will be made by local site staff (except for serious adverse events).

SAE Forms will be emailed directly to the trial office for trial office staff to enter the data on the electronic CRF online. Site staff will be unable to edit this data.

#### 10.3.3 Self-evident corrections

No self-evident corrections will be made to the data.

## 10.4 Data Security

The security of the System is governed by the policies of the University of Birmingham. The University's Data Protection Policy and the Conditions of Use of Computing and Network Facilities set out the security arrangements under which sensitive data should be processed and stored. All studies at the University of Birmingham must be registered with the Data Protection Officer and data held in accordance with the Data Protection Act (2018) and subsequent amendments. The Study Centre has arrangements in place for the secure storage and processing of the study data which comply with the University of Birmingham policies.

The System incorporates the following security countermeasures:

- Physical security measures: restricted access to the building, supervised onsite repairs and storages of back-up tapes/disks in a fire-proof safe.
- Logical measures for access control and privilege management: including restricted accessibility, access-controlled servers, separate storage of non-identifiable data etc.
- Network security measures: including site firewalls, antivirus software, and separate secure network protected hosting etc.
- System Management: the system will be developed by the BCTU Programming Team and will be implemented and maintained by the BCTU Programming Team.
- System Design: the system shall comprise of a database and a data entry application with firewalls, restricted access, encryption and role-based security controls.
- Operational Processes: the data will be processed and stored within the Study Centre (University of Birmingham).
- Data processing: Statisticians will only analyse anonymised data.
- System Audit: The System shall benefit from the following internal/external audit arrangements:
  - Internal audit of the system
  - Periodic IT risk assessments
- Data Protection Registration: The University of Birmingham has Data Protection Registration to cover the purposes of analysis and for the classes of data requested. The University's Data Protection Registration number is Z6195856.

## 10.5 Archiving

The TMF will be stored at BCTU for at least 3 years after the end of the trial. Long-term offsite data archiving facilities will be considered for storage after this time; data will be stored securely and confidentially for at least 25 years. BCTU has standard processes for both hard copy and computer database legacy archiving.

It is the responsibility of the PI to ensure all essential trial documentation and source documents (e.g. signed ICFs, Investigator Site Files, Pharmacy Files, participants' hospital notes, copies of CRFs etc.) at their site are securely retained for at least 25 years.

## 11 QUALITY CONTROL AND QUALITY ASSURANCE

### 11.1 Site Set-up and Initiation

All PIs will be asked to sign the necessary agreements including a site signature & delegation log between the PI and CTU and supply a current CV and GCP certificate to BCTU. All site staff who are performing trial specific tasks are required to sign the **DESTINY Site Signature and Delegation Log**, which details which tasks have been delegated to them by the PI.

Prior to commencing recruitment, each recruiting site will undergo a process of initiation, either a meeting or a teleconference, at which key members of the site research team are required to attend, covering aspects of the trial design, protocol procedures, adverse event reporting, collection and reporting of data and record keeping. Sites will be provided with an Investigator Site File and a Pharmacy File containing essential documentation, instructions, and other documentation required for the conduct of the trial. The BCTU trials team must be informed immediately of any change in the site research team.

### 11.2 Monitoring

The monitoring requirements for this trial have been developed following trial specific risk assessment by BCTU and as documented in the monitoring plan.

### 11.3 Onsite Monitoring

The trial sites will be monitored in accordance with the **DESTINY Monitoring Plan**. Any monitoring activities will be reported to the trials team and any issues noted will be followed up to resolution. Additional on-site monitoring visits may be triggered, for example by poor CRF return, poor data quality, low SAE reporting rates, excessive number of participant withdrawals or deviations (also defined in the monitoring plan). Investigators will allow the DESTINY trial staff access to source documents as requested. The monitoring will be conducted by DESTINY trial manager or other suitable BCTU representative.

### 11.4 Central Monitoring

Trials staff will check incoming ICFs and CRFs for compliance with the protocol, data consistency, missing data and timing at a frequency and intensity determined by the Data Management Plan. Sites will be sent DCFs requesting missing data or clarification of inconsistencies or discrepancies.

Sites will be requested to send in copies of signed ICFs and other documentation for central review for all participants providing explicit consent. This will be detailed in the monitoring plan.

### 11.5 Audit and Inspection

The Investigator will permit trial-related monitoring, audits, ethical review, and regulatory inspection(s) at their site, providing direct access to source data & documents. The investigator will comply with these visits and any required follow up. Sites are also requested to notify BCTU of any relevant inspections.

## 11.6 Notification of Serious Breaches

Sites may be suspended from further recruitment in the event of serious and persistent non-compliance with the protocol and/or GCP, and/or poor recruitment. Any major problems identified may be reported to Trial Steering Committee and the REC. This includes reporting serious breaches of GCP and/or the trial protocol to the REC and MHRA.

In accordance with Regulation 29A of the Medicines for Human Use (Clinical Trials) Regulations 2004 and its amendments, the Sponsor of the trial is responsible for notifying the licensing authority in writing of any serious breach of the conditions and principles of GCP in connection with that trial or the protocol relating to that trial, within 7 days of becoming aware of that breach.

For the purposes of this regulation, a “serious breach” is a breach which is likely to affect:

- the safety or physical or mental integrity of the subjects of the trial
- the scientific value of the trial

Sites are therefore requested to notify the Trials office of any suspected trial-related serious breach of GCP and/or the trial protocol. Where the Trials Office is investigating whether a serious breach has occurred, sites are also requested to cooperate with the Trials Office in providing sufficient information to report the breach to the MHRA where required and in undertaking any corrective and/or preventive action.

## 12 END OF TRIAL DEFINITION

The end of trial will be 6 months after the last data capture, including resolution of data queries and completion of hs-troponin-I sample analysis. This will allow sufficient time for the completion of protocol procedures, data collection and data input. The BCTU trial team will notify the main REC, MHRA and RGT within 90 days of the end of trial. Where the trial has terminated early, the Trials Office will inform the MHRA and REC within 15 days of the end of trial. The Trials Office will provide them with a summary of the clinical trial report within 12 months of the end of trial.

A copy of the end of trial notification as well as the summary report will be sent to the MHRA and REC.

## 13 STATISTICAL CONSIDERATIONS

### 13.1 Sample Size

It is hypothesised that del Nido cardioplegia reduces myocardial injury during surgery compared with St. Thomas' blood cardioplegia. The DESTINY trial will use postoperative hs-troponin-I release to measure the level of myocardial injury which has been shown to strongly correlate with clinical outcomes including inotropic support, duration of ventilation, ventricular dysfunction, and early death [9,21].

The justification for the sample size is based on data from the BRICC trial. In a similar cohort of participants to those in the control group for this study, a mean postoperative hs-troponin release value of approximately 64.0 µg.h/L and a standard deviation of approximately 42.0 µg.h/L were observed.

To detect a difference of 30% (relative reduction, 19.2 µg.h/L absolute reduction) between groups using the standard method of a two-sample t-test and assuming equal variance with 90% power and a type I error rate of 0.05, 102 participants per group will need to be randomised, 204 in total. Assuming and adjusting for a 3% loss to follow-up/drop-out rate (a low rate of drop-out is expected as the primary outcome is measured at 24 hours and it is anticipated that all children undergoing heart surgery would still be in hospital at this point), 220 participants will need to be recruited.

### 13.2 Analysis of Outcome Measures

A separate Statistical Analysis Plan will be produced and will provide a more comprehensive description of the planned statistical analyses. A brief outline of these analyses is given below. The primary comparison groups will be composed of those treated with del Nido cardioplegia versus those treated with St. Thomas' blood cardioplegia. In the first instance, all analyses will be based on the intention to treat principle, i.e. all participants will be analysed in the treatment group to which they were randomised irrespective of compliance or other protocol deviation. For all outcome measures, appropriate summary statistics will be presented by group (e.g. proportions/percentages, mean/standard deviation, or median/interquartile range).

Intervention effects will be adjusted for the minimisation variables listed in section 6.2.1 where possible. No adjustment for multiple comparisons will be made.

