# 1 BACKGROUND AND RATIONALE

## 1.1 Background

### 1.1.1 Cardioplegia in paediatric cardiac surgery

During most surgery for congenital heart disease, it is necessary to stop the heart, allowing access to a still and bloodless field to enable repair of intracardiac defects. Cardioplegia has been fundamental to arresting the heart and protecting against ischaemia-reperfusion (IR) injury during surgery for over 40 years, with approx. 3,500 cardiac surgical operations with cardioplegic arrest performed in children in the UK & Ireland each year [6]. Whilst on cardiopulmonary bypass, a cross-clamp is placed across the proximal aorta and cardioplegia injected into the coronary arteries via the aortic root, leading to electro-mechanical arrest. This reduces myocardial oxygen uptake to only 10% of that of the perfused beating heart, and progressive hypothermia leads to a further stepwise reduction [7]. However, myocardial injury still occurs *routinely* following aortic cross-clamping in children, as demonstrated by the ubiquitous release of troponin after surgery [8,9]. Myocardial protection therefore is a key determinant of heart function and outcome following cardiac surgery.

Current paediatric cardioplegia techniques are primarily derived from adult or laboratory models; however, the immature myocardium has significant structural, physiological, and metabolic differences from the adult heart, including sarcoplasmic reticulum development, mitochondrial density, substrate utilisation, calcium handling and antioxidant defences [3]. It is less tolerant of ischaemia and more sensitive to  $\text{Ca}^{2+}$  overload-mediated injury during reperfusion, particularly with hypoxaemia [10,11]. Myocardial protection that is effective in adults therefore may not be optimal for young children [12,13], especially neonates and those with chronic preoperative cyanosis [14].

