## 6 ENROLMENT AND RANDOMISATION

### 6.1 Enrolment and Screening

Patient eligibility will be confirmed by a member of the research team who is medically qualified, i.e. by a doctor. All baseline assessments will be carried out after informed consent and prior to patient randomisation.

At baseline, prior to randomisation, the following assessments will be performed:

- Patient demographics
- Preoperative weight and height/length
- Resting oxygen saturations
- Preoperative haematocrit
- Comorbidities
- Preoperative medications

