### 6.2 Randomisation

#### 6.2.1 Randomisation Methodology

Participants will be randomised by computer at the level of the individual in a 1:1 ratio to either del Nido cardioplegia or St. Thomas' blood cardioplegia.

A minimisation algorithm will be used within the online randomisation system to ensure balance in the treatment allocation over the following variables:

- Age: neonate (0-30 days), infant (31 days<1 year), child (1<7 years), older child (7<16 years)
- Incision or resection of ventricular myocardium anticipated (yes/no)
- Surgical centre

A 'random element' will be included in the minimisation algorithm, so that each participant has a probability (unspecified here), of being randomised to the opposite treatment that they would have otherwise received.

Full details of the randomisation specification will be stored in a confidential document at BCTU.

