#### 13.2.1 Primary Outcome Measure

AUC for hs-troponin-I release in the first 24 hours (ng/L) will be calculated using the trapezoidal rule from samples taken at baseline, 3, 6, 9, 12 and 24 hours after aortic cross-clamp release.

Missing baseline troponin values will be imputed using the median value of the participant's treatment group. Due to the low variability of the baseline measurements, this should not impact on the validity of the results. To ensure that this is the case, the results from the primary analysis will be compared with that of the complete case, to determine that they are consistent with one another.

Adjusted mean differences along with 95% confidence intervals will be estimated using a linear regression model. Statistical significance of the treatment group parameter will be determined from the p-value generated by the model. If AUC for hs-troponin-I release in the first 24 hours (ng/L) is too skewed, the natural log transformation of the AUC will be used before performing linear regression and the results from this model will be interpreted in the original scale appropriately.

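### The primary troponin model adjusts only for the minimisation variables and omits resting oxygen saturation, a likely prognostic baseline measure: a missed chance of precision, of unknown and possibly small size, not an error

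*Protocol*

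**What the plan says.** Protocol 13.2 gives one covariate rule for all treatment comparisons: "Intervention effects will be adjusted for the minimisation variables listed in section 6.2.1 where possible". Section 6.2.1 lists three such variables. The first is banded age, "Age: neonate (0-30 days), infant (31 days<1 year), child (1<7 years), older child (7<16 years"). The second is "Incision or resection of ventricular myocardium anticipated (yes/no"). The third is surgical centre.

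For the primary outcome, the 24-hour troponin AUC, 13.2.1 says "Adjusted mean differences along with 95% confidence intervals will be estimated using a linear regression model". It provides for a log transformation if the AUC is too skewed. It names no covariate beyond the rule in 13.2.

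Section 6.1 lists "Resting oxygen saturations" among the baseline assessments and fixes their timing: "All baseline assessments will be carried out after informed consent and prior to patient randomisation". Section 1.1.1 explains why the young heart is vulnerable. It refers to "overload-mediated injury during reperfusion, particularly with hypoxaemia" and says that protection suited to adults may not suit young children, "especially neonates and those with chronic preoperative cyanosis".

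**The concern.** The background names two patient features that raise vulnerability to ischaemic injury: immaturity, and hypoxaemia or cyanosis. The first enters both the minimisation and the model. The second enters neither, although it is measured before randomisation and so is a legitimate baseline covariate. Age itself is listed only in bands. The infant band spans about a twelve-fold range of age (31 days to 1 year) and the child band a seven-fold range, so some age-related variation may stay in the residual.

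If saturation or finer age predicts troponin release beyond the minimisation variables, leaving it out makes the primary confidence interval wider than it need be. Eligibility is deliberately wide (1.1.7), so a mix of saturation levels is to be expected. If saturation is not pre-specified, adding it after an imbalance has been seen would look post hoc.

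**Working it through.** **Inputs.** From Protocol 13.1: SD 42.0 µg.h/L, difference 19.2 µg.h/L, 90% power, type I error 0.05 (taken as two-sided), 102 per group. From 6.2.1: 1:1 allocation. The protocol gives no R² for saturation or age, and no SD adjusted for the minimisation variables. Every R² below is therefore an assumption.

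**Step 1: reproduce the plan's figure.** Standardised difference = 19.2 / 42.0 = 0.457. The two-sample t-test (noncentral t) at 90% power gives 101.5, so 102 per group and 204 in total. Power at exactly 102 per group is 90.1%. The stated figure is correct and uses no covariates.

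**Step 2: effect of added covariates.** Residual SD = 42 × √(1 − R²), where R² is the extra share of variance explained. Interval narrowing = 1 − √(1 − R²).

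| Assumed extra R² | Residual SD | Power at 102 per group | Interval narrower by |
|---|---|---|---|
| 0 | 42.0 | 90.1% | 0% |
| 0.02 | 41.6 | 90.7% | 1.0% |
| 0.05 | 40.9 | 91.5% | 2.5% |
| 0.10 | 39.8 | 92.9% | 5.1% |

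**Step 3: allow for what the minimisation variables already explain.** Step 2 treats them as explaining nothing. Suppose instead that they explain 20% (assumed). The SD before any added covariate is 42 × √0.80 = 37.6, and power is already 95.3%. A further 5% of the remaining variance gives SD 42 × √(0.80 × 0.95) = 36.6 and power 96.1%. A further 10% gives SD 42 × √(0.80 × 0.90) = 35.6 and power 96.9%. The power gain falls to about 0.8 to 1.6 points, against 1.4 to 2.8 in Step 2. The proportional narrowing of the interval is unchanged.

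**Step 4: how much the age bands lose.** Ages were simulated uniformly within each band, for four assumed mixes of the bands and five assumed shapes of the age–troponin relation (linear, square root, log, and two exponential decays). The four bands kept about 83% to 93% of the age signal. If age explains a share A of the variance and banding loses a fraction L of that, the partial R² of continuous age over bands is A × L / (1 − A × (1 − L)).

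- A = 0.10, L = 0.05: 0.005 / 0.905 = 0.0055
- A = 0.20, L = 0.10: 0.020 / 0.820 = 0.024
- A = 0.30, L = 0.20: 0.060 / 0.760 = 0.079

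Read against Step 2, most of this range is worth two power points or fewer. A material gain would have to come from saturation, and its contribution given age band, ventricular incision and centre is not in the document.

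**The case against.** The case for leaving the rule alone is substantial.

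- **Validity.** Adjusting for the minimisation variables is sound, and the sample size relies on no covariate gain. This stands in full.
- **Deferral.** Section 13.2 calls itself a brief outline and leaves detail to the SAP, which is not available here and may add covariates or say how age enters. This stands in part. The protocol is not silent, because it states a covariate rule, and an SAP that simply followed the rule would omit saturation.
- **Evidence of prognosis.** Section 1.1.1 speaks of vulnerability and of whether protection is optimal. It does not show that saturation predicts troponin AUC once age band and incision are known. Section 1.1.2 names duration of ischaemia, which is a post-randomisation variable, and the surgical intervention on ventricular muscle, which is already adjusted for. This stands, and it is why no gain can be promised.
- **Scale.** If the AUC is log-transformed, the raw-scale power figures do not carry over directly. This also stands.

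A reader might infer that precision is demonstrably lost, or that a chance imbalance in cyanosis would bias the result. The document supports neither. It gives no R², and under randomisation the confidence interval and error rate already allow for chance imbalance in an unadjusted covariate. A reader might also want the same covariates in the models for LCOS, lactate and omega. Under 13.2.2 the lactate and omega models already take the baseline value where available, and omega is itself computed from arterial saturation. LCOS is binary with an event count that the protocol does not give.

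**Conclusion.** The point holds as a modest recommendation on efficiency. The stated covariate rule leaves out a pre-randomisation measurement that the protocol's own reasoning marks as probably prognostic. The planned analysis remains valid and the 90% power is correct without it.

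For an assumed extra R² of 0 to 0.10, the gain is 0 to 2.8 power points over the unadjusted SD, fewer if the minimisation variables already explain variance, with an interval 0 to 5% narrower. This assumes the raw AUC scale, 102 evaluable children per arm and a roughly linear effect of saturation. The share due to continuous age is probably small. The share due to saturation could be anything from nothing upwards and may overlap with age band and ventricular incision.

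**What to change.** In 13.2.1, carried into the SAP, keep the minimisation factors in the primary model and pre-specify two further covariates before any unblinded analysis: resting oxygen saturation as a continuous term, and age as a continuous term on the log scale. State that a missing saturation is replaced by the median over all participants, not the median of the child's arm, since saturation is recorded before allocation. Limit the change to the primary model and do not extend it to LCOS, lactate or omega.

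The cost is one sentence, no new data, and about two degrees of freedom out of about 200. The downsides are an assumed linear form for saturation and a log-age term correlated with the retained age bands. That correlation affects the age coefficients, which are not of interest, far more than the treatment estimate. If the covariates turn out to be weak, almost nothing is lost.
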